### Expert evaluation of CHW outputs and LLM outputs

12 independent GPs, each with a minimum of 2 years of clinical experience in Rwanda and valid Rwanda Medical and Dental Council licences, will be recruited for this study. They will be organised into four panels of three to evaluate each patient–CHW consultation transcript using a study-specific evaluation rubric (see online supplemental material 1). This evaluation will provide a ground truth against which the LLM and CHW outputs will be measured. Evaluators will receive training to standardise the evaluation approach. This training will include an overview of the study protocol and detailed instructions on using the evaluation rubric. During the training, 10 simulated cases will be reviewed to establish a common frame of reference across the panel and to familiarise evaluators with the rubric.

Everyone in the triplet group of evaluators will independently review the case transcript, make a diagnosis and develop a management plan. The evaluator’s tasks for each objective are as follows:

Based only on the day 0 consultation transcript, a reference standard should be determined to decide on the appropriateness of the CHW and LLM referral decisions.Review the day 0 consultation transcript and the 5-day or 14-day follow-up information to establish a reference standard for evaluating the correctness of the CHW and LLM referral decisions.Assess the diagnostic accuracy of the LLM through:

 Establishing one ‘most likely’ diagnosis based on all the information provided. Independently scoring the appropriateness of the differential diagnosis list according to a prespecified rubric. Assessing whether the diagnosis provided in the counter-referral (or, if unavailable, the panel’s ‘most likely’ diagnosis) is the top-ranked or is included within the top five differential diagnoses suggested by the LLM.

4. Assess the appropriateness of the LLM-generated management plan according to the evaluation rubric.

After the initial assessments, the average response for the Likert scale question will be calculated. The panel will also review and discuss the open-ended responses, such as the ‘most likely’ diagnosis, and collaboratively reach a consensus on the diagnosis.

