### LLM output generation

The recording and transcript will be automatically uploaded and accessed on a secure data warehouse. The first 10–20 transcript samples will be considered a pilot and excluded from the primary analysis. Instead, they will be used to assess recording quality and transcription accuracy, perform exploratory analysis and prompt engineering of the LLM (GPT-4). This process will involve examining the initial transcripts to optimise the LLM’s performance in generating useful outputs and refining how the prompts are structured to elicit the most accurate and relevant responses. By testing and adjusting the prompt structures based on these transcripts, we will effectively ‘tune’ the LLM to improve its clinical decision-making capabilities.

Following this, the research team will omit the interaction’s outcomes (ie, the CHW’s management and referral decision) and feed the transcript and prompts to the LLM to: (1) produce a referral decision, (2) suggest five differential diagnoses in order of likelihood and (3) propose a management plan

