### Primary outcome

The primary outcome of this study is the appropriateness of referral decisions made by CHWs and by the LLM, measured against the consensus decision of an independent expert clinical panel, according to the day 0 consultation transcript only.

For each patient consultation, both the CHW’s actual referral decision on whether to refer the patient to a health facility or manage them in the community and the LLM-generated referral decision will be compared with the reference standard established by a blinded evaluation panel of GPs, based solely on the information available in the day 0 consultation transcript.

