### Data quality assurance

The quality and completeness of all collected data will be routinely monitored by the study management team. Daily data quality checks will be conducted to verify data upload eligibility, completeness and audibility. Cases with missing history and/or referral outcome in the recording will be automatically discarded. Any missing demographic data will be addressed with the respective CHWs via phone call to fill in retrospectively. Only cases that fulfil the above criteria will be forwarded for transcription, translation and LLM prompting. Follow-up adherence will be assessed weekly. Cases that have no follow-up data will not proceed for evaluation. Instead, CHWs will be prompted to conduct the missing follow-up.

A random sample of 20% of audio recordings will be reviewed by independent Kinyarwanda-speaking researchers to cross-validate machine-generated transcripts, with an acceptable error threshold set at <15%. Any breach of this threshold will trigger a data quality review by the study steering committee to determine whether data collection should continue or changes are required.

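### The panel is called blinded, but the procedure described does not secure the reference standard's independence from the CHW's referral decision or, for the fallback diagnosis, from the LLM's list

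*Protocol article*

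**What the plan says.** All places are in the protocol article.

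- **Consultation and related events:** the CHW records the whole consultation.
- **Data quality assurance:** "Cases with missing history and/or referral outcome in the recording will be automatically discarded".
- **LLM output generation:** "the research team will omit the interaction’s outcomes (ie, the CHW’s management and referral decision) and feed the transcript and prompts to the LLM".
- **Expert evaluation of CHW outputs and LLM outputs**, on what the panel reads: "Everyone in the triplet group of evaluators will independently review the case transcript, make a diagnosis and develop a management plan". The first listed task is the day 0 referral reference: "Based only on the day 0 consultation transcript, a reference standard should be determined". Later tasks for the same evaluators are the follow-up-informed reference, a single most likely diagnosis, a rating of the LLM's differential list, a check of whether the reference diagnosis appears on that list, and a rating of the LLM's management plan. Once these individual assessments are complete, the panel discusses its open-ended answers and will "collaboratively reach a consensus on the diagnosis".
- **Primary outcome:** the reference is "established by a blinded evaluation panel of GPs". The strengths box also lists the blinded panel as a strength. Neither place says what the panel is blinded to.
- **Expert evaluation**, task 3: the counter-referral diagnosis is the reference for top-1/top-5 accuracy, and the panel's own diagnosis is used where there is none.

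**The concern.** A reference standard should be set without knowledge of the decisions it will grade. Two routes by which that knowledge could enter are left open.

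**Route 1, primary outcome.** The authors recognised that a transcript discloses what the CHW decided, because they strip it before the LLM sees it. No matching step is described for the panel. A general practitioner who has just read that the CHW referred the patient may be more inclined to agree that referral was appropriate. Both CHW and LLM are scored against the same reference, so a shift towards the CHW raises CHW accuracy and usually lowers LLM accuracy. No later analysis can remove this, because the unshifted reference is never observed.

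**Route 2, secondary outcome only.** The consensus diagnosis is settled after the evaluators have seen and rated the LLM's five differentials. Where no counter-referral diagnosis exists, that consensus is the truth against which the same list is marked. Counter-referral forms are collected for referred patients, so patients managed in the community depend on this fallback.

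**Working it through.** The plan states no figure that tests this point, so the first check is textual.

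**Step 1. Does the source material contain the CHW's decision?** Yes. The whole consultation is recorded, and cases whose recording lacks the referral outcome are dropped.

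**Step 2. Who gets a version without it?** The LLM does, explicitly. For the panel, Study design, Expert evaluation and Primary outcome refer to the consultation or case transcript, with no removal described.

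**Step 3. Does the blinding label settle it?** No. It has no stated object. It fits a redacted panel copy and conflicts with an unredacted one.

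**Step 4. When is each reference fixed?** The day 0 referral reference is the first task and is limited to the transcript. The consensus diagnosis comes after the tasks that score the LLM's list and plan, although each evaluator makes an individual diagnosis first.

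**Step 5. How large could route 1 be?** This is an illustration. The inputs come from Sample size: 73.3% for the CHW (a benchmark figure for GPs, which the plan adopts for CHWs) and 91.2% for the LLM (the GPT-4o figure; the study model is named as GPT-4). Let *a* be the share of CHW-wrong cases in which the panel adopts the CHW's visible decision. The values of *a* are assumptions.

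The decision is binary, so in a flipped case the CHW becomes right, an LLM that was right becomes wrong, and an LLM that was wrong becomes right.

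- CHW wrong: 1 − 0.733 = 0.267
- CHW wrong and LLM right (independent errors): 0.267 × 0.912 = 0.2435
- Both wrong: 0.267 × 0.088 = 0.0235
- Change in CHW accuracy: +0.267*a*
- Change in LLM accuracy: −(0.2435 − 0.0235)*a* = −0.220*a*
- Difference: 0.179 − 0.487*a*

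| *a* | CHW | LLM | Difference (points) |
|---|---|---|---|
| 0 | 73.3% | 91.2% | 17.9 |
| 5% | 74.6% | 90.1% | 15.5 |
| 10% | 76.0% | 89.0% | 13.0 |
| 20% | 78.6% | 86.8% | 8.2 |
| 30% | 81.3% | 84.6% | 3.3 |

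The difference drops below the 11.8 points that Sample size gives as detectable at *a* = (0.179 − 0.118)/0.487 = 12.5%.

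Sensitivity to the independence assumption at *a* = 10%:

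- LLM wrong only where the CHW is wrong: both wrong 0.088, LLM alone right 0.179, loss 0.10 × (0.267 + 0.179 − 0.088) = 0.036, difference 14.3 points.
- Errors never coincide: loss 0.10 × (0.267 + 0.267) = 0.053, difference 12.6 points.

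**Step 6. Route 2.** If a share *s* of the diagnostic cases use the fallback and in a share *d* of those the consensus moves from off the list to on it, top-5 accuracy rises by *s* × *d*. Each 1% of all diagnostic cases moved in this way adds 1 point. The documents give neither *s* nor *d*.

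**The case against.** The strongest reply is that this reads silence as a procedure. The article says twice that the panel is blinded and nowhere says that its copy is unredacted. The retention rule screens recordings, and the study needs the CHW's decision as comparator data, so the rule says nothing about what evaluators are shown. The redaction step is described just before the panel section, so the case transcript there could be the stripped file. The rubric is in the online supplement, which is not shown and may specify both the panel's material and the order of release.

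Most of this stands, and it limits the point. A reader might infer that the GPs do see the CHW's decision and that the primary comparison is therefore biased. The documents do not support that. They show a blinding claim whose object is unstated beside a described procedure that would not deliver it. An unseen supplement may resolve this, but as the article stands the two do not fit together.

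A reader might also infer that the referral reference is settled after exposure to LLM outputs. That is not supported either: the task comes first and is limited to the day 0 transcript, and the later consensus is expressly about the diagnosis.

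Route 2 is further limited because individual diagnoses precede the scoring and a counter-referral diagnosis takes precedence. These reduce the drift but do not rule it out, since the final reference is still the later consensus.

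Finally, the anchoring shares have no source in the documents, and on this model route 1 works against the LLM, so it would not create a false claim of LLM superiority. It would still misstate the primary difference.

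**Conclusion.** The point holds in this form: independence of the reference standard is asserted but not secured by the procedure described.

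- **Primary outcome.** As written, the CHW's decision can reach the panel that judges it. The direction would be a smaller LLM-CHW difference. The size is unknown: 17.9 points falling to about 13.0 (12.6 to 14.3 across error overlaps) holds only if 10% of CHW-wrong cases are anchored and the planning accuracies are right.
- **Secondary outcome.** The fallback consensus diagnosis can drift towards the LLM's list and raise top-1/top-5 accuracy, only in cases without a counter-referral diagnosis and by an amount the documents do not allow one to calculate.

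The sponsor should resolve this explicitly, because the primary outcome rests on the panel and the article presents its blinding as a strength.

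**What to change.** 1. State what the panel is blinded to, and at which stage.
2. For the day 0 referral reference, give the panel the transcript the LLM receives, with the CHW's management and referral decision removed.
3. Record and lock the individual and consensus day 0 referral decisions.
4. Then release the follow-up data, and lock the outcome-informed reference and the consensus diagnosis. Counter-referral information reveals that a patient was referred, so the day 0 lock must come first.
5. Only then show the LLM's differential list and management plan for scoring.

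If this is already the procedure, a sentence in the article pointing to the supplement closes the matter.

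Cost: case material is released in stages, and the consensus discussion moves earlier, ahead of the LLM scoring. The redacted transcript is already produced for the LLM, and no additional evaluators are needed.

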### Secondary outcomes

Compare the appropriateness of CHW referral decisions vs the LLM referral decisions, using the patient’s 5-day or 14-day outcome and counter referral results as the reference standard.

A secondary assessment of referral decision appropriateness will be performed incorporating patient outcomes at day 5 or day 14 follow-up. For each patient, the expert panel will review both the day 0 consultation transcript and subsequent follow-up outcome data to determine whether the initial referral decision was appropriate in retrospect. The CHW and LLM decisions will again be compared with this revised reference standard.

2. Assess the diagnostic accuracy of the LLM as:

Appropriateness of the differential diagnosis list—The expert panel will rate the quality of the LLM-generated differential diagnosis list for each case using a predefined 5-point Likert scale rubric, assessing alignment with medical consensus, knowledge recall, omission of important differentials and inclusion of irrelevant differentials (see online supplemental material 1).Diagnostic accuracy (top-1 and top-5): For consultations where a definitive diagnosis can be established (either via health centre counter-referral or expert panel consensus), the proportion of cases in which the correct diagnosis appears as the LLM’s top-1 diagnosis or within its top-5 ranked differentials will be reported.

3. Assess the appropriateness of the LLM-generated management plan.

The quality of the LLM’s proposed management plans will be independently evaluated by the expert panel using a 5-point Likert scale predefined rubric, rating appropriateness across five domains including alignment with medical consensus, omission of important information, potential for demographic or contextual bias, likelihood of potential harm, contextual appropriateness relative to available resources for CHWs in Rwanda (see online supplemental material 1).

4. Explore the experience and perspectives of patients and CHWs on being recorded during consultation.

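### No day 0 limit is set for rating the LLM's differential list and management plan, so raters may score both knowing the outcome

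*Protocol article*

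**What the plan says.** Under LLM output generation, the research team removes the CHW's management and referral decision and will "feed the transcript and prompts to the LLM to" produce a referral decision, five ranked differentials and a management plan. Neither follow-up nor counter-referral is part of that input.

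Expert evaluation of CHW outputs and LLM outputs then gives the panel four tasks:

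- **First task (primary referral reference):** "Based only on the day 0 consultation transcript, a reference standard should be determined". The Primary outcome section repeats the limit: "based solely on the information available in the day 0 consultation transcript".
- **Second task (outcome-informed referral reference):** "Review the day 0 consultation transcript and the 5-day or 14-day follow-up information to establish a reference standard".
- **Third task (diagnostic accuracy):** the text runs two sub-items together, "diagnosis based on all the information provided. Independently scoring the appropriateness of the differential diagnosis list according to a prespecified rubric". A third sub-item matches the counter-referral diagnosis, or the panel's own diagnosis if there is none, against the LLM's list.
- **Fourth task (management plan):** "Assess the appropriateness of the LLM-generated management plan according to the evaluation rubric".

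Secondary outcomes describes the list rating again: "The expert panel will rate the quality of the LLM-generated differential diagnosis list for each case using a predefined 5-point Likert scale rubric". Its domains include omitted and irrelevant differentials. The domains for the plan include omitted information and likelihood of harm. Data quality assurance adds: "Cases that have no follow-up data will not proceed for evaluation".

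**The concern.** The protocol treats the raters' information as important where referral is concerned: it defines one standard on day 0 information and a separate one made in retrospect. It does not carry that separation over to the two Likert ratings of LLM quality, although the LLM itself saw only the day 0 transcript.

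What is at stake is the meaning of the ratings. A rater who knows the final diagnosis can mark its absence from the list as an important omission even if nothing said on day 0 pointed to it. A rater who knows that the patient recovered, or worsened, can judge the same plan as more or less harmful. The list rating would then move towards the top-5 hit rate, which is already reported separately, and would say less about whether the list was reasonable given what was known. A reader of the results could not tell day 0 quality from quality judged with hindsight.

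**Working it through.** No arithmetic applies. The check sets the information base stated for each judgement beside what the LLM had.

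| Judgement | Information base stated in the article |
|---|---|
| LLM's own output | Day 0 transcript, CHW decision removed, plus prompts |
| First task: primary referral reference | Day 0 transcript only |
| Second task: revised referral reference | Day 0 transcript plus day 5 or day 14 follow-up |
| Third task: most likely diagnosis | Everything provided |
| Third task: rating of the differential list | None stated; a rubric is named |
| Third task: top-1/top-5 match | Counter-referral diagnosis, otherwise the panel's |
| Fourth task: rating of the management plan | None stated; a rubric is named |

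1. **Is a day 0 limit stated elsewhere for the two ratings?** No. Neither Secondary outcomes nor Secondary outcome analysis gives one.

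2. **Is later information available when the ratings are made?** Follow-up exists for every evaluated case, because cases without it are held back from evaluation. This shows that the data are in hand. It does not show when raters see them. No sentence withholds them until the ratings are complete.

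3. **Where do the ratings stand in the list?** Both come after the task that opens follow-up. The list rating also sits between a diagnosis made on all information and the comparison with the counter-referral. Followed in the printed order, the list and the plan are scored by someone who has already looked at the outcome.

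4. **Does the averaging step separate them?** Only in part. The Likert responses are averaged after the initial assessments, and the panel then discusses the open-ended answers and agrees a diagnosis. That puts the ratings before the consensus diagnosis. It does not put them before the follow-up, which each evaluator needs for the second task.

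5. **Is the later information even across cases?** No. Under Follow-up and related events, counter-referral details are collected for referred patients, and forms are uploaded where received. What a rater knows therefore depends partly on the CHW's referral decision. The ordinal models adjust for consultation features and include a random intercept for clustering; rater knowledge is not named among the adjustments.

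6. **Which domains are exposed?** Mainly omission, irrelevance and harm. Demographic or contextual bias and fit to the resources CHWs have depend much less on outcome.

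**The case against.** The strongest reply is that the article is silent here rather than wrong. The phrase about all the information belongs grammatically to the most likely diagnosis; scoring the list is a separate sub-item. The tasks are set out by objective, not as a dated sequence. Evaluators are described as reviewing the consultation transcript, and follow-up is named where it is meant to be used but not in the text on the two ratings. The rubric and its instructions are in supplemental material that is not shown, and a form could well fix what raters see at each item.

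Most of this stands, and it rules out a stronger reading. A reader might infer that the raters already hold the outcome and that both ratings do judge the LLM on information it never had. The document does not say so; it leaves the matter open. A reader might also infer a bias between paper and app cohorts. That would need rater knowledge, for example through counter-referral return, to differ between cohorts, and nothing in the document says that it does. Nor is an LLM-versus-CHW comparison affected here, since only the LLM is rated on these two outcomes.

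The reply does not remove the point. The article itself fixes the information base for both referral judgements and for the diagnosis, leaves it open for these two ratings, and lists them after outcome-informed work. This is more than a detail left to a form, because the order as printed allows hindsight into domains that are sensitive to it.

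Using later information for the top-1/top-5 reference diagnosis is legitimate and is not criticised.

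**Conclusion.** The concern holds as a weakness in the order and information base of two secondary outcomes: the differential-list rating and the management-plan rating. As listed, the procedure permits raters to score both with knowledge of the outcome, and with more knowledge for referred patients whose counter-referral was returned. It does not establish that they will.

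No size can be given. The document offers no figure for how often later information could not have been foreseen on day 0, or for how far it would move a score. Good and bad outcomes may push ratings in opposite directions, so the net direction is unknown too.

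The conclusion assumes that evaluators follow the tasks in roughly the printed order and that the unseen rubric does not already impose a different one. If it does, only the article's wording needs attention. The stated day 0 basis of the primary outcome is untouched. The change should be made, because it is cheap and ratings already given with the outcome known would be hard to undo.

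**What to change.** Work in two stages within the existing evaluation:

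1. **Day 0 stage.** From the day 0 transcript alone, the rater records the referral judgement of the first task, then scores the differential list and the management plan. Entering the referral judgement first keeps sight of the LLM's output from colouring the primary reference. All these entries are locked.
2. **Full-information stage.** Follow-up and any counter-referral are then released for the revised referral reference, the most likely diagnosis and the top-1/top-5 match.

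State this order in the protocol. If the rubric already sets it, one sentence saying so is enough. If ratings have already been made with follow-up visible, report them as hindsight ratings and not as day 0 quality.

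The cost is one ordered, locked step on the evaluation form, with the same raters and the same cases.

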### Consultation and related events

On consent, the CHW will initiate audio recording of the entire clinical consultation using the StudyApp. CHWs will be instructed to conduct consultations according to their usual practice, guided either by the national CHW decision-making algorithm (on paper or via CHWApp). The consultation recording—and all subsequent LLM outputs—will not be used to influence the care of the patient. The CHW will be asked to provide their usual standard of care, and there are no restrictions placed on that care as a result of this study. Following the consultation, CHWs will administer a brief structured patient experience questionnaire to assess perceptions of being recorded (see online supplemental material 1).

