### Follow-up and related events

As part of standard CHW practice, patients will be followed up on day 5 to assess symptom progression and treatment outcomes. In addition, the study protocol includes a day 14 follow-up for research purposes. CHWs will complete a structured follow-up form (see online supplemental material 1) on the StudyApp, capturing information on symptom resolution (resolved, unchanged, worsened, deceased), any further health service use and counter-referral details for referred patients.

Patients reporting full symptom resolution at the day 5 follow-up will not undergo the day 14 follow-up. CHWs will also photograph and upload any counter-referral forms (providing feedback to the CHW for continued care in the community) received from health centres for referred patients (see online supplemental material 1).

After the data collection period, RAs will conduct short user experience surveys and four focus group discussions of 8–12 CHWs to get insight into their experience of being recorded and any challenges faced (see online supplemental material 1).

Patient participant flow is summarised in figure 1.

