### Secondary outcome analysis

Referral decision appropriateness will be reassessed following integration of day 5 and day 14 follow-up outcome data. The expert panel’s revised appropriateness assessment incorporating these outcomes will serve as an updated reference standard. Diagnostic accuracy metrics and paired comparisons will be repeated against this outcome-informed standard.

For cases with a definitive diagnosis established through expert panel consensus or counter-referral documentation, the proportion of correct diagnoses appearing as the LLM’s top-1 and within its top-5 differential diagnosis list will be reported, with 95% CIs.

Outcomes of interest (appropriateness of differential diagnosis and appropriateness of management plan) will each be measured on a 5-point Likert scale. Distributions of these Likert scale responses will be displayed using frequency tables, numerically summarised across interactions using the median, along with upper and lower quartile values, and visualised using histograms, demonstrating the proportion of interactions rated to be at each level of the scale. For each secondary outcome separately, a multilevel ordinal regression model will be fit, adjusting for important consultation features, with a random effect on the intercept term to account for the natural clustering of the data, as discussed above. Secondary outcome involving measuring the top-1 and top-5 diagnostic accuracy for a subset of participants where a definitive diagnosis was made. The mean (median) rank of the ground truth diagnosis in the differential list will also be summarised.

The patient and CHW user experience questions will be analysed with descriptive analysis to assess the acceptability and impact of recordings. Qualitative responses from CHWs will be thematically analysed to generate themes.

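### Top-1 and top-5 diagnostic accuracy pools two non-interchangeable reference diagnoses, on a 'definitive' subset that the panel fallback does not imply

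*Protocol article*

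**What the plan says.** The rule for the reference diagnosis is in the protocol article under *Expert evaluation of CHW outputs and LLM outputs*. The evaluators' task is "Assessing whether the diagnosis provided in the counter-referral (or, if unavailable, the panel’s ‘most likely’ diagnosis) is the top-ranked" or lies within the top five. The fallback, "if unavailable, the panel’s ‘most likely’ diagnosis", carries no further condition on the case. The panel's own diagnosis is described there as "Establishing one ‘most likely’ diagnosis based on all the information provided", and after the individual assessments the panel is to "collaboratively reach a consensus on the diagnosis".

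Under *Follow-up and related events*, counter-referral forms are those "received from health centres for referred patients". Under *Consultation and related events*, the recording and the LLM output "will not be used to influence the care of the patient", so whether a patient is referred is the CHW's decision alone.

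*Secondary outcomes* defines the denominator: "For consultations where a definitive diagnosis can be established (either via health centre counter-referral or expert panel consensus"). *Secondary outcome analysis* reports one top-1 and one top-5 proportion with a 95% CI over both sources, and describes the analysis as being "for a subset of participants where a definitive diagnosis was made". It adds a mean (median) rank of the ground-truth diagnosis, which rests on the same mixed reference. No section says what makes a diagnosis definitive.

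**The concern.** Which reference a case receives depends on how the patient was managed. A facility diagnosis requires that the CHW referred the patient and that a form was returned and uploaded. Patients kept in the community, and referred patients without a form, are graded against the panel. This is differential verification: two references of different kind, applied to groups that differ in how they were selected, then averaged with weights set by the referral rate and the return of forms.

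The single proportion then has no fixed meaning outside this sample. The same LLM with the same accuracy in each group could show a different pooled value where CHWs refer more often or forms come back more reliably.

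The denominator raises a second question. If the panel's consensus diagnosis is the fallback for any case without a counter-referral, no evaluated case needs to leave the analysis. Two other sections nevertheless speak of a restricted set, with no criterion for membership. Two analysts could follow the text and obtain different denominators.

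**Working it through.** The article states no expected accuracy, referral rate, form-return rate or subset size for this outcome, so there is no figure to reproduce. Every accuracy and share below is an assumption. Only the planned 800 consultations come from the article (*Sample size*).

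**Pooled value.** Let *w* be the share of analysed cases with a counter-referral diagnosis, *aF* the LLM's accuracy against the facility diagnosis in those cases, and *aP* its accuracy against the panel diagnosis in the rest. Then

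pooled = *w* × *aF* + (1 − *w*) × *aP*,

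and moving *w* from 0.2 to 0.6 changes it by 0.4 × (*aF* − *aP*). For *aF* = 0.50 and *aP* = 0.70:

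- *w* = 0.2: 0.2 × 0.50 + 0.8 × 0.70 = 0.66
- *w* = 0.6: 0.6 × 0.50 + 0.4 × 0.70 = 0.58

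| *aF* | *aP* | *w* = 0.2 | *w* = 0.6 | Shift (points) |
|---|---|---|---|---|
| 0.70 | 0.70 | 0.70 | 0.70 | 0 |
| 0.60 | 0.70 | 0.68 | 0.64 | −4 |
| 0.50 | 0.70 | 0.66 | 0.58 | −8 |
| 0.70 | 0.50 | 0.54 | 0.62 | +8 |

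The last row shows that the sign depends on which group has the higher accuracy. The article does not settle that.

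**Yardstick.** At a proportion of 0.6 with all 800 consultations and no clustering, the 95% CI half-width is 1.96 × √(0.6 × 0.4 / 800) = 0.034, or 3.4 points. A 10-point gap therefore produces a shift slightly larger than the sampling uncertainty, and a 20-point gap more than twice as large. Clustering or a smaller subset would widen the interval.

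**Denominator.** Suppose *w* = 0.4 and *aF* = 0.50, and that 60% of panel-graded cases are called definitive, with accuracy 0.80 in those and 0.50 in the others.

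- 'Definitive' subset: (0.4 × 0.50 + 0.6 × 0.6 × 0.80) / (0.4 + 0.6 × 0.6) = 0.488 / 0.76 = 0.642
- All evaluated cases: 0.4 × 0.50 + 0.6 × (0.6 × 0.80 + 0.4 × 0.50) = 0.608

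The difference is 3.4 points. If every panel-graded case counts as definitive, the two denominators coincide and the difference is zero.

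**The case against.** Taking the facility diagnosis where it exists and the panel's otherwise is a prespecified best-available hierarchy, and a breakdown by source could sit in a full analysis plan that is not shown. The outcome is secondary, descriptive and for the LLM only. The article plans no comparison of it between districts or over time, and the study will have just one realised counter-referral share. All of this stands, and it limits the importance of the point. It does not remove it, because what the article fixes is the mixed reference and the pooled proportion, and a missing table is not the complaint.

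Four stronger readings are tempting and are not supported:

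- A reader might infer that the pooled figure reflects case mix instead of the LLM. At any fixed share it rises and falls with the LLM's accuracy, and with equal accuracies the share has no effect.
- A reader might infer that the panel sees only the transcript the LLM saw. Its diagnosis rests on all the information provided, and under *Data quality assurance* cases without follow-up data do not proceed to evaluation.
- A reader might infer that the panel-graded part flatters the LLM. No passage fixes the direction of any bias.
- A reader might infer that hard cases are dropped. *Secondary outcomes* counts panel consensus as one route to a definitive diagnosis, so few or no cases may be lost. The supported point is that the sections do not agree.

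The CHW's decision is also not the whole selection mechanism. Referral is necessary for a counter-referral diagnosis, but some referred patients will have no form and will be graded against the panel.

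**Conclusion.** The point holds for the secondary top-1/top-5 outcome and for the rank summary that uses the same reference. Two non-interchangeable references are pooled, and which one applies depends on the CHW's referral and on the return of a form. The pooled figure therefore depends on the counter-referral share as well as on the LLM whenever accuracy differs between the two groups. The size is unknown: 0, 4 or 8 points for assumed gaps of 0, 10 or 20 points and a share moving from 20% to 60%.

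The 'definitive' restriction is undefined and does not follow from a rule that gives every evaluated case a fallback diagnosis. Its effect could be nil or, under the assumptions shown, about 3 points. The primary outcome uses the panel's day 0 standard throughout and is untouched.

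**What to change.** 1. Report top-1 and top-5 separately by reference source, with the number of cases in each.
2. Also report both against the panel's consensus diagnosis for all evaluated consultations, as a common reference. A gap between the two sources could come from the reference or from the patients, and this helps to tell them apart.
3. Use all evaluated consultations as the main denominator. Define 'definitive' and keep that subset as a sensitivity result.
4. Reconcile the wording in *Expert evaluation of CHW outputs and LLM outputs*, *Secondary outcomes* and *Secondary outcome analysis*.
5. Show agreement between panel and counter-referral diagnoses only for cases where the panel reached its diagnosis without sight of the counter-referral. The information given to the panel may include that form, and agreement would then be partly circular. For the same reason, state what the panel saw when presenting item 2.

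The cost is a few table rows, more than one accuracy figure to explain, and a small extra task: evaluators now match the LLM list to the panel diagnosis only when no counter-referral is available, and would have to do so in counter-referral cases too.
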